#### Primary and secondary endpoints

Baseline sample characteristics will be shown for all randomized patients treatment-wise and for pooled data. For categorical variables, category frequency counts and percentages will be shown. For continuous variables, the arithmetic mean, median, 1st and 3rd quartiles, minimum and maximum values will be presented. Follow-up data will be given in line plots allowing visual comparisons between treatment groups.

#### Primary analysis

For the primary endpoint “rate of moderate or severe postoperative complication or death within 28 days post surgery,” the fixed effect of treatment and the random effect of clinic and the treatment slope will be estimated by a binary logistic regression model. The resulting odds ratio with corresponding 95% confidence intervals (CI) and *p* values will be tabulated. Estimated marginal frequencies and their 95% CIs will be presented graphically. Superiority of the individualized hemodynamic therapy is considered established if the upper margin of the 95% CI of the corresponding odds ratio lies below 1.

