#### Inclusion criteria

To ensure the presence of marked surgical trauma, open visceral, urological, and gynecological surgery are covered by this study. Expected duration of surgery must be ≥ 120 min and the requirement of volume therapy must be expected to be ≥ 2 l. Risk for any postoperative complications must be ≥ 10% as assessed preoperatively by the ACS-NSQIP (American College of Surgery – National Surgical Quality Improvement Program, www.acsnsqip.org) risk calculator [4, 18, 19].

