#### Secondary endpoints

Secondary endpoints are: (1) the number of moderate and severe postoperative complications in total, per patient and for each individual complication; (2) the occurrence of at least one of these complications on days 1, 3, 5, 7, and 28 in total and for every complication. The additional secondary endpoints include (3) days alive and free of mechanical ventilation, vasopressor therapy and renal replacement therapy, length of ICU and hospital stay at day 7 and day 28 further characterize perioperative morbidity and its socioeconomic impacts. (4) For the assessment of quality of life, an interview (personal or by telephone) based on the EQ-5D-5L™ questionnaire [23] is performed at the time point of enrollment and 6 months after surgery. Mortality is assessed 6 months after surgery. All the secondary endpoints mentioned above will be recorded at the defined time points, but will be analyzed at the end of the study.

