### Sample size calculation and statistical analysis

#### Sample size

According to previous published data [24] assessing the impact of hemodynamic goal-directed therapy, we assume that the primary outcome will occur in 48% of the control group and in 33% of the intervention group. The null hypothesis of the study is that individualized, goal-directed therapy does not lead to a statistically significant difference in morbidity and mortality at day 28 after major abdominal surgery. Assuming in this null hypothesis (H0) that the two groups are not significantly different from each other at the significance level α = 0.05 with respect to the primary outcome, 334 patients are required to have an 80% chance of detecting a difference between the control group and the experimental group of 15%. Therefore, 167 patients per group would have to be enrolled into the study. Taking into account a dropout rate of about 10% and exclusion of the first two patients in every center, a number of *n* = 380 patients is necessary.

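### The primary model could adjust for the ACS-NSQIP risk already required at entry: a cheap gain in power, not an error

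*Protocol article*

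**What the plan says.** The Primary analysis section of the protocol article lists the terms of the primary logistic model: "the fixed effect of treatment and the random effect of clinic and the treatment slope will be estimated". Treatment is the only fixed effect. Superiority is declared if the upper 95% confidence limit of the resulting odds ratio is below 1. The Secondary analyses section names no baseline covariate either.

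The Inclusion criteria section states: "Risk for any postoperative complications must be ≥ 10% as assessed preoperatively by the ACS-NSQIP" risk calculator. The Study population section requires all inclusion criteria to be met at screening, before enrolment. An individual predicted risk must therefore be worked out for every patient before randomisation.

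The Randomization section describes 1:1 allocation in blocks of 6, with balance over centres and arms. It does not mention baseline risk.

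The Sample size section plans an unadjusted comparison of two proportions: "we assume that the primary outcome will occur in 48% of the control group and in 33% of the intervention group", and "334 patients are required to have an 80% chance of detecting a difference between the control group and the experimental group of 15" percentage points.

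**The concern.** A prognostic baseline value that eligibility requires for every patient is not used in the primary analysis. The planned power is 80% with no reserve. A covariate that predicts the outcome would raise power at the same sample size, and it would correct the treatment estimate for any chance difference in baseline risk between the arms. The article fixes the terms of the primary model and ties the success rule to it, so this is a comment on a stated choice rather than on missing detail. What is at stake is efficiency: a few points of power, depending on how well the score predicts the endpoint.

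**Working it through.** **Inputs from the protocol article**
- Event risks 48% and 33%, and 167 per group: "167 patients per group would have to be enrolled into the study" (Sample size).
- Significance level: "at the significance level α = 0.05 with respect to the primary outcome". Two-sidedness is not stated. The two-sided formula gives 334 and the one-sided formula gives 264, so two-sided is implied.
- Six centres (Study design).

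**Assumptions, not in the documents**
- Discrimination of the score for the primary endpoint: AUC varied from 0.50 to 0.76.
- Between-clinic SD of 0.3 on the logit scale (second run only).

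**Step 1: reproduce the planned figure.** With p̄ = (0.48 + 0.33)/2 = 0.405:

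n = [1.96·√(2·0.405·0.595) + 0.8416·√(0.48·0.52 + 0.33·0.67)]² / 0.15² = [1.361 + 0.577]² / 0.0225 ≈ 166.9

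This rounds up to 167 per group, 334 in total, an exact match; power at 167 per group is 0.800. The total also follows. The text reads "Taking into account a dropout rate of about 10% and exclusion of the first two patients in every center", and 334 × 1.1 + 2 × 6 = 379.4, hence 380. The 80% therefore belongs to an unadjusted comparison and does not rely on adjustment.

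**Step 2: power with and without the score.** The data model is logit P(event) = a + t·treatment + g·x, with x a standard normal score. For each g, a and t were solved so that the marginal risks stay at 48% and 33%. Each setting had 6,000 simulated trials of 334 patients. Success was log OR + 1.96·SE < 0. The simulation error of one power value is about √(0.8·0.2/6000) = 0.005. There were no clinic effects.

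| AUC (assumed) | Unadjusted power | Adjusted power | N giving the unadjusted power once adjusted |
|---|---|---|---|
| 0.50 | 0.800 | 0.796 | 334 |
| 0.56 | 0.799 | 0.799 | 331 |
| 0.60 | 0.795 | 0.802 | 324 |
| 0.65 | 0.800 | 0.825 | 313 |
| 0.70 | 0.809 | 0.853 | 297 |
| 0.76 | 0.799 | 0.873 | 274 |

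From AUC 0.60 to 0.76 the gain is worth 334 − 324 = 10 to 334 − 274 = 60 patients.

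A separate simulation, also without clinic effects, gave adjusted against unadjusted power of about 80% vs 80% at AUC 0.57, 81% vs 79% at 0.63, 85% vs 81% at 0.69 and 86% vs 80% at 0.74.

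**Step 3: add clinics and the entry cut-off.** Six clinic intercepts were added to the data and the fitted models, and the score was cut off below 10% predicted risk and entered as a logit (8,000 trials per setting). The paired gains were +0.5, +1.4, +3.4, +5.1 and +7.4 points at AUC 0.56, 0.60, 0.65, 0.70 and 0.75. The random treatment slope was not simulated in any run.

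**Step 4: scale of the odds ratio.** The planned marginal odds ratio is (0.33/0.67)/(0.48/0.52) = 0.534, a log odds ratio of −0.63. At AUC 0.70 the same marginal risks correspond to a conditional odds ratio of 0.490. The standard error of the log odds ratio rises from 0.227 to 0.244, but the estimate moves further from zero by more. The gain is therefore in the test, not in a narrower interval for the odds ratio.

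**Step 5: chance imbalance.** With 167 per arm, the standardised difference in the score has standard error √(2/167) = 0.109. A difference of at least 0.2 SD has |z| ≥ 0.2/0.109 = 1.83, which occurs in about 7% of trials. If the score has SD 0.75 on the logit scale (assumed; AUC about 0.69), such an imbalance shifts the log odds ratio by about 0.2 × 0.75 = 0.15. That is 0.15/0.63, or about a quarter of the planned effect.

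**The case against.** The strongest reply is that nothing here is wrong. Leaving out a baseline covariate does not bias a randomised comparison or invalidate its test, and the analysis matches its own sample size calculation. That stands. A reader might infer that the trial is underpowered or its primary test unsound because of the omission; Step 1 shows otherwise.

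Several other limits also stand.
- The documents give no discrimination figure. At AUC 0.60 or below the gain is about 1 point or less.
- It is tempting to call the score the strongest known predictor, or to say that baseline risk varies widely. The article says neither. The 10% floor, the restriction to open major surgery and the exclusions may narrow the spread. The score predicts any complication, whereas the endpoint is moderate or severe complications or death by day 28.
- The marginal frequencies planned under Primary analysis come from a model without covariates, so covariate-standardised risks would be new.
- The text makes the score an eligibility check and does not say that the number is stored.
- The simulations leave out the random treatment slope, so their absolute power is not that of the planned model.
- A reader might extend the point to EQ-5D-5L, since the interview "is performed at the time point of enrollment and 6 months after surgery". The article fixes no model for that outcome, so there is nothing to correct.

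The reply that covariates may be left to an analysis plan carries less weight, because the article itself names the terms of the primary model and the success rule.

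**Conclusion.** This is a worthwhile improvement, not an error. The unadjusted primary analysis is valid and consistent with the planned 80%. Adjustment for the ACS-NSQIP risk would raise power at 334 patients by 0 to 1 point (AUC up to 0.60), about 1 to 3 points (0.63 to 0.65), 4 to 5 points (0.70) or 6 to 7 points (0.75). It would also remove the effect of chance imbalance in baseline risk. If the score has no prognostic value the cost is within simulation error (0.800 vs 0.796). The direction is firm. The size rests on the assumed AUC and on models without the random treatment slope.

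**What to change.** - Confirm that the eCRF stores the numeric ACS-NSQIP risk and not only the eligibility check. If it does not, add the field.
- Before outcome data by arm are seen, pre-specify logit(ACS-NSQIP predicted risk) as a continuous fixed covariate in the primary logistic model, next to the terms already named.
- State that the odds ratio in the success rule is then conditional on baseline risk.
- Add covariate-standardised marginal risks by arm and their difference, with 95% confidence intervals.
- Keep the odds ratio without the score as a sensitivity analysis.

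The cost is wording and possibly one eCRF field, with no new visit, measurement or patient. If only the eligibility check was kept, values for patients already enrolled must be retrieved from screening records. The conditional odds ratio lies further from 1 than the unadjusted one, so it must be read with the standardised risk difference.

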#### Secondary analyses

The composite endpoint “occurrence of moderate or severe postoperative complication or death” and the secondary endpoints “postoperative morbidity,” “occurrence of moderate or severe complications,” “occurrence of individual complications” and “number of complications per patient” will be analyzed via longitudinal binary logistic regression models, treating clinic, treatment slope and patient within clinic as random effects. Treatment, frequencies over time (FU) and their interaction will be considered fixed effects. Odds ratios, their 95% CIs and *p* values will be tabulated. Estimated marginal FU and their 95% CIs will be presented graphically.

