### Primary and secondary outcomes

#### Primary endpoint

Considering the high relevance for the individual patient and for society, the postoperative outcome is most appropriately reflected by a combination of morbidity and mortality. Therefore, the primary endpoint is a composite comprising the rate of patients with one or more moderate or severe postoperative complications or death within 28 days post surgery. Moderate and severe postoperative complications are defined by 22 single-organ outcome failures based on a consensus statement of the European Society of Anesthesiology (ESA) – European Society of Intensive Care Medicine (ESICM) joint taskforce on perioperative outcome measures [22]. A summary of the included organ failures and the severity grading is given in Additional file 5: Table S2.

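### The number of complications per patient is a count, but the plan assigns it to a binary logistic model reported as odds ratios

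*Protocol article*

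**What the plan says.** The Secondary endpoints section lists two different kinds of outcome. The first is a quantity: "the number of moderate and severe postoperative complications in total, per patient and for each individual complication". The second is a yes/no status: "the occurrence of at least one of these complications on days 1, 3, 5, 7, and 28". The Primary endpoint section says that complications are "defined by 22 single-organ outcome failures", so the count can run from 0 to 22 if each listed outcome is counted once.

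The Secondary analyses section then puts all of these, together with the composite that contains death, into one model class. The sentence opens with "The composite endpoint “occurrence of moderate or severe postoperative complication or death” and the secondary endpoints" and ends its list with "number of complications per patient” will be analyzed via longitudinal binary logistic regression models". The random structure is given by "treating clinic, treatment slope and patient within clinic as random effects", and the fixed effects by "Treatment, frequencies over time (FU) and their interaction will be considered fixed effects". The results to be tabulated are odds ratios with confidence intervals and p values. No count model, rate ratio or mean ratio is named.

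The article does not say whether the status at each visit day is cumulative to that day, new since the last visit, or present on that day. It also does not say how a patient is coded after death.

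**The concern.** A binary logistic model needs a 0/1 response. Following the text, the analyst must cut the count at some value, and no value is given. The obvious cut, one or more, turns the number of complications into the occurrence of any complication, which the same sentence already lists. The endpoint then adds no information of its own. A therapy that halved the number of complications among affected patients, without changing how many patients were affected, would show no effect.

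The patient random effect raises a separate question. Under cumulative coding, a patient who has had the event stays at 1 at every later visit. A random-intercept logistic model is unstable on such data, so it matters which coding is meant.

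**Working it through.** **The plan's own figure.** The Sample size section assumes 48% against 33%, 80% power and α = 0.05. With pooled variance:

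n = [1.960·√(2·0.405·0.595) + 0.842·√(0.48·0.52 + 0.33·0.67)]² / 0.15² = (1.361 + 0.577)² / 0.0225 ≈ 167 per group, 334 in total.

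The stated figure reproduces, and nothing below alters it.

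**Count endpoint: what a cut at one or more ignores.** Let P0 be the share of patients with no complication and m the mean count. First events per patient number 1 − P0, so the share of complications that are second or later is 1 − (1 − P0)/m. For the control arm take P0 = 1 − 0.48 = 0.52. This is a stand-in, because the 48% belongs to the composite with death. The article gives no count distribution, so three are assumed:

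| Assumed distribution | Mean m | Share ignored |
|---|---|---|
| Poisson | −ln 0.52 = 0.65 | 1 − 0.48/0.654 = 27% |
| Negative binomial, dispersion 1 | 1/0.52 − 1 = 0.92 | 1 − 0.48/0.923 = 48% |
| Negative binomial, dispersion 2 | (0.52⁻² − 1)/2 = 1.35 | 1 − 0.48/1.349 = 64% |

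The reverse view gives the same message. With variance m + m²/k, assumed means of 0.65 (near Poisson), 1.0 (k = 0.95) and 1.5 (k = 0.4) give 47.8%, 49.5% and 46.4% of patients with at least one complication. Means that differ by a factor of 1.5/0.65 = 2.3 look almost the same to the binary model.

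**Repeated outcomes, cumulative coding.** Assumed control risks by days 1, 3, 5, 7 and 28 are 15, 25, 33, 38 and 48%. Intervention risks are these times 0.33/0.48, with 167 patients per arm. The model has treatment, visit, their interaction and a patient random intercept; clinic effects are left out. It was fitted by maximum likelihood with the patient SD held fixed:

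| Patient SD | Log-likelihood | Day-28 odds ratio |
|---|---|---|
| 1 | −711.1 | 0.44 |
| 5 | −472.4 | 0.11 |
| 10 | −442.6 | 0.017 |
| 20 | −433.2 | 0.0004 |
| 40 | −431.5 | 1.7 × 10⁻⁷ |
| 80 | −431.4 | 2.9 × 10⁻¹⁴ |

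The likelihood keeps rising and has no interior maximum. Its ceiling is the saturated value, 167·Σ p ln p summed over the six possible first-event outcomes in each arm. That is −240.0 − 191.4 = −431.4, and it is approached only as the SD grows without limit. The marginal day-28 odds ratio is (0.33/0.67)/(0.48/0.52) = 0.53.

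**Repeated outcomes, interval coding.** Assumed new-event rates per visit are 15, 12, 10, 8 and 18% in control and 0.6 times these in the intervention arm, with a true patient SD of 1. Log-likelihoods at SD 0.5, 1, 1.5 and 2 are −538.4, −533.8, −538.0 and −547.6. The maximum is near 1, with odds ratios of about 0.54 to 0.60. With an assumed 4% of patients dying and coded 1 from death onward, the values at SD 1, 1.5 and 2 are −587.2, −583.6 and −588.8. The maximum is near 1.5, with odds ratios of about 0.52 to 0.64. Here the model can be fitted.

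**The case against.** A journal article condenses the full protocol, and an analysis plan may hold the detail. That defence covers the visit coding and the handling after death, which the article leaves unstated. It does not cover the count: the article names a model class and an effect measure for it, and they do not fit the endpoint. One charitable reading is an item-level binomial model over the 22 outcomes, but the listed effects contain no item term.

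Four stronger readings are tempting, and the document does not support them:

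- **That the model cannot validly estimate any of these repeated outcomes.** The divergence needs cumulative coding. The 28-day window of the primary endpoint and the single day-28 determination for discharged patients make that coding natural, but it is never stated. Death as an absorbing state does not by itself prevent a finite fit.
- **That the dichotomised count duplicates the primary endpoint.** The primary includes death; the count does not. What is repeated is a secondary endpoint.
- **That the longitudinal odds ratio would contradict the primary one.** A patient-conditional odds ratio lies further from 1 than the odds ratio of the primary model, which has no patient effect. It answers a different question in the same direction. The plan also promises estimated marginal frequencies. This does not rescue the cumulative case, where the conditional odds ratio has no stable value.
- **That models for single complications would fail to converge.** Sparse events are plausible, but the article gives no event rate for any single complication and no fit was tested.

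**Conclusion.** The mismatch between the count endpoint and the binary model holds as stated text and should be corrected. The ignored share, about 27% to 64% of control-arm complications, is illustrative. It rests on the three assumed distributions, on a cut at one or more, and on borrowing 52% event-free from a composite that includes death.

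The point on repeated outcomes holds conditionally: estimates degenerate under cumulative coding and are finite under interval coding. Those results rest on assumed visit-specific rates and a model without clinic effects.

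The reach is limited to secondary analyses. The primary model uses one binary outcome per patient with no patient random effect.

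**What to change.** Take the number of complications per patient out of the binary logistic sentence. Analyse the count to day 28 with a count model, for example negative binomial or Poisson with robust variance, with treatment and clinic as terms. Report a rate or mean ratio with its 95% confidence interval.

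For the outcomes at days 1, 3, 5, 7 and 28, state whether the status is cumulative, new since the last visit, or present on the day, and how patients are coded after death. If it is cumulative, replace the patient random-effect model by marginal logistic models (GEE), separate logistic models per visit, or a first-event analysis. If it is interval coded, the stated model can remain.

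The cost is analysis-plan wording and model code. No new data are needed, and neither the sample size nor the primary analysis changes.

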## Discussion

Reduction of perioperative mortality and morbidity is greatly required due to the massive benefit for the patients and the health care system. In Europe, overall mortality after surgery has been reported to be up to 4% [2] and after high-risk surgery or in high-risk patients it has to be assumed to be even higher. Morbidity or postoperative complications, which are potentially triggered by inadequate oxygen supply to the peripheral organs, have to be seen as the primary cause for reduction of quality of life and the immense health care costs ensuing. Every percentage point reduction of postoperative complications could save approximately 180 million to US$270 million [5]. In a recent multi-center trial the achievement of adequate preoperative oxygen delivery was associated with a lower postoperative morbidity compared to the standard of care [25]. In this context a various number of meta-analyses evaluating the impact of hemodynamic goal-directed therapy, and thereby optimizing oxygen supply, have already demonstrated reduction of morbidity in patients undergoing high-risk surgery [12–17]. However, meta-analyses are frequently limited in their statement due to inhomogeneity in population and therapeutic approaches. In published trials, stroke volume or cardiac output have been predefined, standardized and generalized to a total cohort of patients not taking into account the single patient’s individual cardiovascular needs and capacities. In the largest randomized multi-center study on goal-directed therapy published so far, the focus of the intervention protocol was maximization of stroke volume by repetitive fluid administration without using functional parameters of preload supplemented by a fixed dose of inotropes. In this trial the focus was put on maximizing stroke volume. However, this large multi-center trial did not significantly reduce the composite primary endpoint of morbidity and mortality [26]. In contrast to this approach, in the iPEGASUS trial, the protocol is not targeting a maximized stroke volume. In the iPEGASUS trial, individual CI assessment is primarily based on PPV-guided volume status optimization followed by defining the achieved CI as “individually optimized CI” under optimized volume status conditions. This “individually optimized CI” is used as the CI target during the total perioperative period and volume and inotrope application is only performed when this “individually optimized CI” is not reached.

The hypothesis of the planned clinical trial is that perioperative hemodynamic optimization, based on the novel approach of individualization of hemodynamic therapy, can reduce postoperative morbidity and also mortality. A previous study focusing on a PPV-guided CI individualization and, in contrast to iPEGASUS, using PPV-based volume loading, even when the individualized CI was reached, demonstrated a reduction in postoperative complications [24]. However, this finding is now evaluated in a larger randomized controlled, multi-center study using a modified intervention protocol. Thus, in the proposed study, hemodynamic therapy is tailored individually to each patient, based on optimization of fluid status by the functional parameter PPV and based on this individually titrated goal of CI. Individualization of therapy is a key factor for successful treatment, especially when reduction of morbidity and mortality is targeted. Therefore, the iPEGASUS trial further develops the concept of hemodynamic goal-directed therapy to individually set goals and is designed to assess its impact on mortality and morbidity.

